**TOTAL BUDGET SPEND IN NORTHERN INSTITUTIONS* US$465,093**

**INSTITUTION WHERE GRANT TO BE HELD:**

London School of Hygiene & Tropical Medicine

**AIMS OF THE ACT CONSORTIUM THIS PROJECT ADDRESSES***

1. Improving access.

To evaluate alternative models of ACT delivery involving public sector providers, private facilities, retailers, community health workers and mothers/caretakers so as to maximise access to effective antimalarial drugs for those who have malaria.

1. Improving drug targeting.

To determine the impact on antimalarial drug use and health outcomes of interventions to improve rational drug prescribing and dispensing, including use of rapid diagnostic tests, so as to minimise over-diagnosis of malaria and over-prescription of antimalarial drugs

**SUMMARY:**

Most malaria deaths occur within 48 hours of onset of symptoms, and in rural areas with poor access to health facilities, home management of malaria (HMM) can improve the timeliness of treatment and reduce malaria mortality by up to 50%. In order to maximize both coverage and impact, artemisinin combination therapies (ACTs) should be deployed in HMM programmes, as well as in formal health facilities. Up to 80% of malaria cases are treated outside the formal health sector and shops are frequently visited as the first (and in some cases only) source of treatment. Strategies to deploy ACTs in Africa thus also need to examine the role of shops in home management and to ensure that drugs sold are appropriate. The current practice of presumptive treatment of any febrile illness as malaria (both at health facilities and in the context of HMM) based solely on clinical symptoms without routine laboratory confirmation, results in significant over-use of antimalarial drugs. With ACT being a more costly regimen, it is important to be more restrictive in its administration and rapid diagnostic tests (RDTs) provide a simple means of confirming malaria diagnosis in remote locations lacking electricity and qualified health staff.

This study therefore proposes to evaluate the feasibility, acceptability, and cost-effectiveness of using RDTs to improve malaria diagnosis and treatment by two types of community-based providers:

(a) community drug distributors and (b) local drug shops.

The accuracy of RDTs, and the acceptability of this approach, will be evaluated in both low and high transmission areas.

**RESEARCH PROPOSAL (Maximum 10 pages - font size 11):**

**(a) Background to the study. Maximum 1 page**

The main component of the current malaria control strategy in Sub-Saharan Africa is to reduce malaria-related mortality and severe morbidity through early diagnosis and effective case management. The majority of *Plasmodium falciparum* malaria deaths occur within 48 hours of onset of symptoms, and in rural areas with poor access to health facilities treatment is often given too late. Home management of malaria (HMM) improves the timeliness of treatment and has been shown in field trials to reduce malaria mortality by up to 50%. Large-scale research studies have also shown that scaling up HMM is both feasible and effective.1 Strategies to deploy ACTs need to investigate the feasibility of incorporating the use of ACTs into HMM programmes, in order to maximize both coverage and impact on malaria morbidity and mortality.

In much of Africa, up to 80% of malaria cases are treated outside the formal health sector and polypharmacy is common.2 Factors affecting low utilization of formal health facilities include distance, waiting time, disrespectful behaviour of staff towards patients, and drug stockouts. In comparison, shops selling antimalarial drugs are more numerous, more easily accessible, and more oriented to satisfying consumer needs. As such, these shops are frequently visited as the first (and in some cases the only) source of treatment.3-5 Strategies to deploy ACTs in Africa also need to take into account the role of shops in home management of malaria and to ensure that drugs sold are appropriate.

The current practice of presumptive treatment of any febrile illness as malaria (both at health facilities and in the context of HMM) is based solely on clinical symptoms without routine laboratory confirmation and results in over-use of antimalarial drugs.6 The higher cost of ACTs and uncertainties that supply can meet global demand necessitates a change in diagnostic approach to reduce over-diagnosis and misuse of the new generation of antimalarial drugs.7-10 Rapid diagnostic tests (RDTs) can be used to confirm malaria infection and are very simple to use, require minimal training and may prove cost-effective in the context of ACT.11-13 With the majority of malaria cases being ‘self-diagnosed’ by the patient and treated with drugs purchased from a local shop,3,4 changes in diagnostic practice are not only needed amongst health-care providers, but also amongst patients themselves, pharmacies and other drug sellers. The availability of diagnostic confirmation in drug shops may increase willingness to pay for new ACT treatments. Reducing over-prescription of costly ACTs should offset the increased costs of diagnosis, however the cost-effectiveness of this approach will depend largely on the local prevalence of malaria.

We therefore propose to examine the cost-effectiveness of ACT in the home management of malaria (HMM-ACT) in a range of transmission settings, including both high and low transmission, comparing two approaches:

1. current practice where HMM is based on clinical symptoms without any laboratory confirmation, and
2. HMM following rapid diagnostic test (RDT).

The research will be undertaken in two geographically distinct but complementary studies, which will investigate the cost-effectiveness of introducing RDTs into:

- HMM-ACT administered by trained community-based distributors, in two districts of rural Uganda to compare cost-effectiveness in an area of high, perennial transmission and an epidemic-prone area of low and seasonal transmission.
- Local drug shops in a rural district of Uganda with a wide choice of treatment providers.

This proposal thus comprises of two work packages. The second work package in which the use of RDTs by shop keepers is evaluated is described below.

In both studies clinical, economic and socio-behavioural analyses will be undertaken to provide a comprehensive evaluation of the interventions to improve quality of diagnosis and treatment. Methods of evaluation will be standardized across the two sub-studies to ensure comparability of findings. The results of these studies will help policy makers to make a decision on the deployment of ACTs and RDTs in home-based management of malaria. The data generated will help identify the most appropriate strategy for a range for epidemiological settings. Research findings will also help identify how to achieve maximal coverage of correct and appropriate malarial treatment and to minimize misuse of this valuable new drug combination.

WORK PACKAGE II:

Introducing rapid diagnostic tests (RDTs) into the private health sector in Uganda: a randomised trial among registered drug shops to evaluate impact on antimalarial drug use

**Lead PI:** [name]

**(b) Aim and objectives**

**Aim:** This study aims to examine the feasibility of introducing RDTs into registered drug shops in Uganda to encourage rational drug use in case management of malaria,with a focus on the correct use and adherence to ACTs. Study outcomes will assess drug prescription practices in drug shops and public health services, as well as treatment-seeking behaviour by local communities, including sources of drug treatment, consumer preferences, demand for improved diagnosis, and use of ACTs. The study also examines differences in utilization between households and ability of the approach to improve quality of diagnosis and treatment, especially amongst the poorest members of society.

It is hypothesised that the use of diagnostic testing will reduce over-diagnosis and over-prescription of antimalarial drugs in the private sector. It is further hypothesised that the availability of diagnostic testing in drug shops and confirmation of malaria will increase uptake and sale of ACT combinations (rather than monotherapy or cheaper, less efficacious, antimalarial drug combinations), and may also encourage purchase of the full treatment dose, as well as patient adherence to the full course of ACT treatment.

**Primary objectives**

1. To evaluate the impact of availability of RDTs in the commercial sector

- on appropriate antimalarial drug sales in the commercial sector (incl. consumer demand, treatment advice given in registered drug shops)
- on appropriate antimalarial drug prescription in cases referred to the formal health sector

1. To describe and quantify treatment-seeking behaviour under a scenario of ACT provision in both the commercial and formal health sectors, including identification of choice menus, initial source of treatment, antimalarial drugs used and economic costs.

**Secondary objectives**

1. To assess perceptions and acceptability of the use of RDTs among malaria patients and drug providers.
2. To assess the impact of improved malaria diagnosis on ACT adherence among providers and consumers.

**(c) Study design and methods**

***Study design***

A cluster-randomized trial of RDTs in registered drug shops in a rural area of Mukono District, an area of high transmission in Central Uganda. Numerous sources of malaria treatment can be found in the area, including government health facilities, licensed pharmacies, trained community distributors of pre-packaged drugs (Homapak) for home management of malaria, registered drug shops and unlicensed shops selling drugs.

### As the study aims to evaluate consumer preferences, treatment actions and demand for improved malaria diagnosis in the private sector, treatment options are designed to mimic current choices. Communities resident within the study area will thus be able to seek ACT treatment from a range of providers including government health facilities, local pharmacies and registered drug shops (some of which will offer improved diagnosis through use of a RDT), as shown in the table below.

### The study will be undertaken in two sub-counties, and census enumeration areas will be randomized to either intervention or control. Registered drug shops located in intervention areas will receive training in the use of rapid diagnostic test for malaria (RDTs) and supplied with RDTs by the research team, and trained to only recommend antimalarial treatment with Coartem® after a positive test result. In the control areas, registered drug shops will continue to dispense antimalarial treatment based on presumptive diagnosis (current practice).

### RDTs have recently been introduced into government health facilities in Uganda. Government health staff in the study area will therefore receive additional supportive training to use RDTs and to only provide treatment with Coartem® after a positive result. The study will ensure that public health facilities are well stocked with RDTs, antimalarials and other essential drugs through the government credit supply system. Community sensitization meetings will be carried out to increase awareness of ACTs, reasons for the new treatment policy for malaria, the need for better diagnosis, and importance of adherence to treatment.

| **Private facilities (pharmacies and drug shops)** |
| --- |
| Drug shops randomised to either:  1) Confirmatory diagnosis with RDTs, followed by sale of a commercially-available ACTs only to those who have a positive RDTs  **or**  2) Current practice:  Presumptive clinical diagnosis and treatment of fever |

*Key strengths to the study site*

- - Multiple sampling points within the same district and health system
  - Study design allows comparison between private and public health care providers to assess patient preferences

This allows direct comparison of the effectiveness of treatment, and the cost-effectiveness of improved diagnosis, in a range of different health care providers within the same country.

*Primary endpoints*

- Proportion of patients receiving appropriate treatment from a commercial drug outlet: % of patients diagnosed with malaria who receive appropriate[[1]](#footnote-2) ACT treatment (irrespective of time since onset of treatment).
- Over-prescription: % of patients, who are not parasite-positive, who receive inappropriate ACT treatment from a commercial drug outlet.
- Provider adherence to RDT result: % of patients who receive appropriate treatment, consistent with RDT result
- Cost-effectiveness of RDT compared to presumptive treatment in home management of uncomplicated malaria.

All endpoints will be examined and reported according to age and sex: children aged 0-4y, 5-15y and adults ≥ 16y. For each age group, the proportion of patients receiving appropriate treatment will be compared between shops with RDTs and shops without RDTs, in order to determine whether diagnostic testing reduces overuse of antimalarials in that age group.

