Patients are free to choose which shops they use, and will be able to choose between outlets that offer diagnostic testing and those that do not, as this service will be openly advertised. Patients seeking treatment for uncomplicated malaria (or fever) from a registered drug shop in the intervention areas will be offered a RDT prior to drug purchase. Verbal consent will be sought from patients accepting the test, to also prepare a blood film from the fingerprick blood sample for the purposes of the research. Patients who decline an RDT test (and patients seeking treatment at registered drug shops in non-intervention areas) will receive presumptive treatment, as per current practice. This outcome (no test) will be recorded and whether an antimalarial was purchased or not.

Community sensitization on the need for treatment of febrile illness within 24 hrs after onset of illness will also be carried out. Sensitization meetings will also aim to increase awareness of ACTs within the community, the need for better diagnosis, and the importance of adherence to treatment.

*Referral mechanism of severe malaria and non-malarial fevers*

Severe malaria: Children with danger signs consistent with suspected severe malaria (WHO definition 2000) will be given pre-referral treatment using a rectal artesunate suppository and referred immediately to the nearest health unit for further treatment. Patients will be referred using an emergency referral form, including details of symptoms and the use of pre-referral treatment. Shops will keep a dated register for referrals and copy of the referral form with personal identifiers (also at health units).

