### *Sample size requirements*

### Sample size requirements for a cluster-randomised trial15 were calculated for the primary endpoint of the proportion of patients receiving appropriate treatment (in line with parasitological status). Appropriate treatment is defined as a composite including both a) those who are slide-positive who purchase an ACT and b) those who are slide-negative who do not purchase an ACT or other antimalarial drug. As the priority for improving treatment in the private sector is to increase the proportion of true cases that purchase and use an ACT (as opposed to antipyretics only, without any antimalarial treatment), we do not include prompt appropriate treatment within 24 hours as the primary endpoint in this work package.

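### The first primary endpoint contradicts itself: its listed wording counts patients diagnosed with malaria, an arm-dependent group, while its footnote and the sample size section score all patients against the research slide

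*Protocol*

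**What the plan says.** Protocol, Primary endpoints, first bullet: the endpoint is given as "Proportion of patients receiving appropriate treatment from a commercial drug outlet: % of patients diagnosed with malaria who receive" appropriate ACT treatment. The bullet does not say who makes the diagnosis or how.

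The design table just above it describes the two arms by how they diagnose. Intervention shops use "Confirmatory diagnosis with RDTs, followed by sale of a commercially-available ACTs only to those who have a positive RDTs". Control shops use "Presumptive clinical diagnosis and treatment of fever". Under Diagnosis and treatment procedures there is a third group: "Patients who decline an RDT test (and patients seeking treatment at registered drug shops in non-intervention areas) will receive presumptive treatment". Intervention clients who decline the test are therefore handled as control clients are.

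Three other places define the same endpoint differently:

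- Footnote 1, attached to the word appropriate in that bullet, takes the research blood slide as reference. It counts slide-positives given a first-line antimalarial and slide-negatives not given one.
- Appropriateness of treatment and/or referral repeats that composite.
- Sample size requirements names the proportion of patients treated in line with parasitological status as the primary endpoint that was sized: "Appropriate treatment is defined as a composite including both a) those who are slide-positive who purchase an ACT and b) those who are slide-negative" and buy neither an ACT nor any other antimalarial.

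The third primary endpoint reads "Provider adherence to RDT result: % of patients who receive appropriate treatment, consistent with RDT result". Only intervention shops are supplied with RDTs.

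**The concern.** A slide-negative client who correctly leaves without an antimalarial is a success under the footnote. Under the bullet that client is not a success, because no ACT was received, and may not be counted at all, because no malaria was diagnosed. The two definitions therefore give different numerators and different denominators for the endpoint on which the trial was sized.

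The literal version matters because membership of its denominator is decided after randomisation by the process under test. In control shops it would hold clients presumed to have malaria. In intervention shops it would hold RDT-positives plus decliners. Filtering one arm's denominator through a test raises the share of true cases in it, so the arms can differ even if sellers treat clients identically. Dispensers are to record a diagnosis, with the RDT result where there is one, so the data would allow an analyst to follow the literal wording.

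**Working it through.** **The plan's own figure.** The sample size section gives 10 clusters per arm for m = 61 consultations per cluster, 90% power, k = 0.25, p0 = 0.50 and p1 = 0.75. I read the significance level as two-sided 0.05.

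c = (1.960 + 1.282)² × [p0(1−p0)/m + p1(1−p1)/m + k²(p0² + p1²)] / (p1 − p0)²
= 10.507 × [0.00410 + 0.00307 + 0.0625 × 0.8125] / 0.0625 = 9.74, so 10.

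The stated 10 is reproduced by the form without an added cluster (adding one gives 10.74). It is not in dispute here. The populations are: the 50% baseline is ACT purchase over all consultations, while the 75% target is among RDT-positives, a group that control shops cannot identify.

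**Literal reading when selling does not change.** Assumptions, none given in the protocol:

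- parasite prevalence π = 20, 40, 60 or 80%
- RDT sensitivity Se = 95%, specificity Sp = 90%
- no decliners
- every control client presumed to have malaria
- ACT sold to 50% of clients in both arms whatever the test shows, and no other antimalarial sold

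The numerator is slide-positive patients who get an ACT. The denominator is patients diagnosed with malaria.

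- Control: 0.50 × π.
- Intervention: 0.50 × PPV, with PPV = Se·π / [Se·π + (1 − Sp)(1 − π)].
- At π = 20%, PPV = 0.19/0.27 = 0.704, so intervention is 35.2% against 10% in control.

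| π | PPV | Control | Intervention | Gap (points) |
|---|---|---|---|---|
| 20% | 0.704 | 10% | 35.2% | 25.2 |
| 40% | 0.864 | 20% | 43.2% | 23.2 |
| 60% | 0.934 | 30% | 46.7% | 16.7 |
| 80% | 0.974 | 40% | 48.7% | 8.7 |

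With Se = 90% and Sp = 80%, intervention is 26, 38, 44 and 47%, so the gap runs from about 17 points to 7.

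**Composite over all patients, same scenario.** π × 0.50 + (1 − π) × 0.50 = 50% in both arms at every prevalence. There is no artefact.

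**Footnote scoring applied only to the diagnosed.** Use the planning rates: ACT to 75% of RDT-positives, 20% of RDT-negatives and 50% of control clients, with Se = 95% and Sp = 90%. Intervention restricted to RDT-positives is PPV × 0.75 + (1 − PPV) × 0.25. Over all patients it is π(0.95 × 0.75 + 0.05 × 0.20) + (1 − π)(0.10 × 0.25 + 0.90 × 0.80). Control is 50% either way.

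| π | All patients | Diagnosed only |
|---|---|---|
| 30% | 73.8% | 65.1% |
| 60% | 73.2% | 71.7% |
| 80% | 72.7% | 73.7% |

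The choice of denominator moves this version of the endpoint too, but its size and direction depend on prevalence.

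**The case against.** The best defence is that the intended endpoint is clear. The slide composite appears in the footnote, in the evaluation section and in the sample size section. The text after the primary endpoints says the proportion is compared between shops to see whether testing reduces overuse, which makes sense only for the composite. This largely stands: the protocol does contain an endpoint that is comparable between arms. What the defence does not do is repair the bullet. The footnote explains appropriate, not diagnosed, and leaves a denominator that cannot hold the composite it defines.

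A reader might go further and infer that the randomised comparison is broken as planned. The documents do not support that, because the comparable composite is the one named for sizing. A reader might also infer that the endpoint rewards over-treatment in control shops. That requires ignoring the footnote, and over-prescription in patients who are not parasite-positive is a primary endpoint in its own right. Nor is the count of four primary endpoints an error. The sample size section identifies the one that was sized, and how several are handled can be left to the analysis plan.

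Two further limits stand. Decliners are treated presumptively, so the intervention denominator is not RDT-positives alone, and the literal gap shrinks as more clients decline. The protocol also does not say that every febrile control client is recorded as having malaria.

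**Conclusion.** The point holds as an internal contradiction in the definition of the sized primary endpoint. The bullet and the three slide-based statements cannot all be followed, and the bullet read literally yields an arm-dependent denominator fixed after randomisation. Under the stated assumptions that reading produces a gap of about 25 points at 20% prevalence, falling to 9 at 80%, with no change in what is sold; the composite produces none. The range rests on assumed RDT accuracy, no decliners, all control clients presumed to have malaria, and equal 50% sales. It illustrates the hazard of the wording and does not predict the trial's bias. The correction is needed because the sentence is wrong as written, and rewording deals with most of it.

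**What to change.** 1. Reword the first primary endpoint to match the sample size section: among all enrolled clients seeking treatment for fever or suspected malaria in either arm, the proportion treated in line with the research slide result, compared by randomised arm.
2. Align the footnote, the evaluation section and the sample size section. The first two count slide-negatives not given a first-line antimalarial; the third counts those who buy no antimalarial at all. State the baseline and target rates for the same population. With a perfectly accurate RDT the planning rates give a composite of 76 to 79% (0.75π + 0.80(1 − π), π from 80% to 20%), above the 75% used. At Se 95% and Sp 90% it is about 73 to 74%, so the calculation should be rechecked.
3. Replace the diagnosed-with-malaria wording in the two secondary endpoints that use it, prompt effective treatment and equity of treatment.
4. Reconcile the slide-collection statements. Slides are described for antimalarial-treated patients, for test accepters in intervention shops, and for exit-interview patients in control areas. An intervention client who declines the test and buys no antimalarial has no stated slide. One rule must apply in both arms, or slide availability will itself differ by arm.
5. State that provider adherence to the RDT result is descriptive and confined to the intervention arm, since control shops have no RDT.

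The cost is rewording, plus a uniform slide rule that may add some slides. The number of primary endpoints may stay as it is.

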***Evaluation***

*Appropriateness of treatment and/or referral*

Prescription patterns and drug sales in private shops and clinics will be measured through the use of exit interviews, drug sales records and mystery shopper visits. Drug sales records will be adapted to include data on RDT results. Semi-structured exit interviews will be used to ascertain whether diagnostic testing was offered, was accepted by the patient, and type and quantity of drugs sold. Exit interviews will also investigate the patient’s perception of diagnostic testing and their knowledge and understanding of the test result, treatment advice and/or referral. In non-intervention areas, a finger-prick blood sample will be taken to prepare a research blood film to ascertain by microscopy whether the fever was due to malaria. A random sample of patients will also be followed at home after several days to ascertain adherence to treatment (see section below), outcome of the illness and total household expenditure on treatment. Patients will be recruited on exit from the drug outlet and individual informed consent will be sought from patients (parents or guardians, in the case of minors) to participate in an exit interview and any subsequent household visits.

The appropriateness of treatment provided will be evaluated as the proportion of correctly treated malaria cases, based on the “gold standard” of the research blood slide read by an experienced research technician. Appropriate treatment of fever is a composite definition including both a) those who a slide-positive who are given a 1st-line antimalarial and b) those who are slide-negative who are not given a 1st-line antimalarial. Over-prescription will also be assessed as the proportion of children who are not parasite positive who receive inappropriate ACT treatment.

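### The over-prescription endpoint counts only ACT, although the hypothesis is about antimalarials in general, so it can understate or miss a change in overuse

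*Protocol*

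**What the plan says.** The Protocol describes overuse in several places, and the drugs counted are not the same.

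- **(b) Aim and objectives**, first hypothesis: "It is hypothesised that the use of diagnostic testing will reduce over-diagnosis and over-prescription of antimalarial drugs in the private sector". This covers antimalarials in general. The second hypothesis expects sales to move towards ACT from monotherapy and cheaper combinations, so the authors presuppose that non-ACT antimalarials are being sold.
- **(c) Study design and methods, Primary endpoints**: "Over-prescription: % of patients, who are not parasite-positive, who receive inappropriate ACT treatment from a commercial drug outlet". The numerator is ACT only.
- **The paragraph after the primary endpoints**: appropriate treatment is compared between shops with and without RDTs by age group, "in order to determine whether diagnostic testing reduces overuse of antimalarials in that age group". This is again antimalarials in general.
- **Evaluation, Appropriateness of treatment and/or referral**: "Over-prescription will also be assessed as the proportion of children who are not parasite positive who receive inappropriate ACT treatment". The numerator is ACT only, and the population is now children.
- **Sample size requirements**: the slide-negative half of the appropriate-treatment composite is "those who are slide-negative who do not purchase an ACT or other antimalarial drug". This covers any antimalarial.
- **Footnote 1 to the primary endpoints, and Evaluation**: the slide-negative half of the same composite excludes only a first-line antimalarial.

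Among the secondary endpoints, the referral item looks at the absence of any antimalarial sale, but only in RDT-negative patients.

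**The concern.** A slide-negative client who leaves the shop with monotherapy or an older combination has been overtreated in the sense of the first hypothesis, but is not a case of over-prescription under the endpoint. If non-ACT sales were negligible this would not matter. The second hypothesis says that they are not, and that testing may change the drug mix.

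The endpoint therefore mixes two things: how often slide-negative patients are sold an antimalarial, and what share of those sales is ACT. A change in either moves it. The trial could understate a real fall in overuse, miss it, or credit itself with a fall when sellers have only replaced ACT with another drug. The referral endpoint cannot fill the gap, because untested control clients have no RDT result and so offer no comparison.

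**Working it through.** **The plan's own figure.** Inputs from Sample size requirements: 50% against 75%, 61 consultations per cluster, k = 0.25, 90% power and 5% significance (read as two-sided). The standard formula for proportions in a cluster-randomised trial, with no extra cluster added, is

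c = (1.96 + 1.28)² × [(p0(1−p0) + p1(1−p1))/m + k²(p0² + p1²)] / (p0 − p1)².

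With unrounded normal quantiles the first factor is 10.507. The bracket is (0.25 + 0.1875)/61 + 0.0625 × (0.25 + 0.5625) = 0.05795. So c = 10.507 × 0.05795 / 0.0625 = 9.74, that is, the stated 10 clusters per arm. This point does not rest on a sample size error.

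**What the endpoint measures.** For one arm, let a be the proportion of slide-negative patients sold any antimalarial and s the share of those sales that is ACT. Then

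ACT-only over-prescription = a × s.

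**Inputs.** I take a = 50% in control and 20% in intervention areas, the baseline and target in Sample size requirements. Using them this way is an assumption: the 50% is labelled there as ACT purchase, and the 20% refers to RDT-negative patients. The shares s are not in the Protocol, so a range is shown. The true change is 50% − 20% = a 30-point fall.

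| ACT share, control | ACT share, intervention | ACT-only, control | ACT-only, intervention | Change read |
|---|---|---|---|---|
| 100% | 100% | 50% | 20% | −30 points |
| 50% | 50% | 25% | 10% | −15 points |
| 80% | 100% | 40% | 20% | −20 points |
| 60% | 100% | 30% | 20% | −10 points |
| 50% | 100% | 25% | 20% | −5 points |
| 40% | 100% | 20% | 20% | 0 |

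The reading is zero when 0.50 × s(control) = 0.20 × s(intervention), that is, when the control share is 0.4 times the intervention share. With an all-ACT intervention arm this is 40%.

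**Equal and unequal shares differ.** With equal shares the absolute change shrinks, but the ratio of the two arms stays at 0.20/0.50 = 0.4 (10%/25% = 0.4). With unequal shares the ratio is distorted as well: at 60% against 100% it is 20%/30% = 0.67.

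**Power.** Use 10 clusters of 61 per arm and k = 0.25 in the formula above. Any antimalarial, 50% against 20%, has power above 99.9%. ACT-only with equal 50% shares (25% against 10%) keeps 99.9%. ACT-only with an all-ACT intervention arm has 76% at a 60% control share and 30% at a 50% control share. These figures treat all 61 patients per cluster as slide-negative, so they are optimistic.

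**The opposite error.** Suppose any-antimalarial use is 50% in both arms, all ACT in control and 40% ACT in intervention. ACT-only reads 50% against 0.50 × 0.40 = 20%, an apparent 30-point fall with overuse unchanged.

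**The case against.** Five arguments for the present wording deserve weight.

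1. **ACT may be the right target.** The background rests on ACT cost, supply and misuse, so an ACT-specific measure is defensible. This stands as a reason to keep the ACT-only figure. It does not make that figure a test of antimalarial overuse.

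2. **The drug switch concerns confirmed malaria.** A reader might infer that the two hypotheses push the endpoint in opposite directions and that the conclusion on overuse would have the wrong sign. The Protocol does not support that. It ties the move to ACT to testing and confirmation of malaria, while the endpoint is limited to patients who are not parasite-positive. A rise in ACT among them would need false-positive RDTs, sales against the result, or ACT sold to clients who decline the test. All are possible, but the last group is treated as in current practice, so its drug mix should resemble control. An all-ACT intervention arm is therefore an extreme case.

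3. **ACT promotion may reach both arms.** It is tempting to say that only sellers in RDT shops are trained on Coartem. The opening paragraph of Diagnosis and treatment procedures describes such training for private providers without limiting it by arm, and community sensitisation is not limited either. This narrows the likely gap in ACT share.

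4. **Overuse is not judged on this endpoint alone.** The age-group comparison uses appropriate treatment, and the sample size version of that composite counts any antimalarial in slide-negative patients. That is a partial safeguard. But footnote 1 and Evaluation narrow it to first-line drugs, and a composite with slide-positive patients does not isolate overuse.

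5. **The second hypothesis is not without an endpoint.** The first primary endpoint covers ACT treatment in diagnosed patients, and an equity endpoint reports ACT by socio-economic group. What is missing is only a split into ACT, other antimalarial and none.

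Breakdown tables could be left to an analysis plan. The definition of a primary endpoint is fixed here, and it disagrees with the hypothesis and with the sample size section.

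**Conclusion.** The point holds as a mismatch between endpoint and hypothesis. The over-prescription endpoint ignores non-ACT antimalarials sold to slide-negative clients, while the hypothesis, the stated purpose of the age-group comparison and the sample size section all concern antimalarials in general.

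On the 50% and 20% rates, a true 30-point fall reads as anything from the full 30 points to zero over the mixes tabulated. Equal shares shrink the absolute fall but leave the ratio intact. The more serious distortion needs shares that differ between arms, and reading zero needs a large difference. If nearly all antimalarials sold in both arms are ACT, the two definitions agree. Attenuation is likelier than a reversal, so this is a change that should be made rather than a flaw that invalidates the trial.

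**What to change.** - In Primary endpoints and in Evaluation, define over-prescription as the percentage of slide-negative patients sold any antimalarial, ACT or other, in the same patient population in both places.
- Report the ACT and non-ACT components by arm. This keeps the ACT-only figure for the cost and supply question.
- Use one slide-negative definition in Primary endpoints, footnote 1, Evaluation and Sample size requirements.
- Optionally, tabulate ACT, other antimalarial and none among slide-positive patients by arm, so that the second hypothesis can be read directly.

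The cost is endpoint wording and one table. Exit interviews already record "type and quantity of drugs sold", and the present endpoint already needs the parasite status. No extra patients or visits are needed.
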